### Sample size calculation

#### Clients

A 50% consent rate is estimated from the 250 eligible clients passing through the Central Coast DACS within the study timeframe (N = 125). Previous research conducted by the authors has achieved consent rates of 50% for participants recruited from the general community [e.g. via media advertisements, 16]. We obtained higher consent rates (i.e. 82%) when previously recruiting directly from DACS 
[16], however we have estimated our sample size recruitment rates based on the lowest figure. Previous research with the target population has resulted in an 80% retention rate over a 15-week period 
[16], translating to a final projected sample size of 100 retained participants at the 15-week follow-up for the current study.

#### Clinicians

All clinicians working with the Central Coast DACS are invited to participate in the study, providing a maximum of 19 clinician participants for the trial. Assuming clients are distributed equally between the clinicians, each clinician will see 13 clients during the study period (250/19). Service data from the Central Coast DACS indicate the average occasion of service for clients engaged with the service is three sessions. Assuming a 50% compliance rate with completion of session checklists by clinicians, we estimate having a pool of 342 session checklists for analysis.

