**Methods/design:**

19 clinicians within an AOD service on the Central Coast of New South Wales, Australia, will be recruited to the trial. Consenting clinicians will participate in a baseline focus group discussion designed to explore their experiences and perceived barriers to adopting innovation in their clinical practice. Computer comfort and openness to innovation will also be assessed. Throughout the trial, current, new and wait-list clients will be referred to the research program via the clinical service, which will involve clients completing a baseline and 15-week follow-up clinical assessment with independent research assistants, comprising a range of mental health and AOD measures. Clinicians will also complete session checklists following each clinical session with a client, outlining the extent to which the SHADE computer program was used. Therapeutic alliance will be measured at intake and discharge from both the clinician and client perspectives.

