#### Clinicians

At information sessions conducted by the authors, clinicians in each team associated with the DACS were introduced to the study and asked to provide consent to participate. Participation involves five activities:

(1) Completion of a baseline focus group discussion regarding the use of innovation in clinical practice.

(2) Completion of a baseline questionnaire regarding their openness to innovation and computer comfort.

(3) Use of the SHADE treatment program with new and ongoing clients in whatever manner they choose, with delivery of the DVD content of the program either contained within the clinic session or provided to clients to complete in their own home in between clinic sessions.

(4) Referral of contact details for new and ongoing clients to the client-data-collection phase throughout the study period, regardless of their exposure to the SHADE treatment program.

(5) Completion of session checklists (see Appendix A) following every counselling session with new and ongoing clients, regardless of their exposure to the SHADE treatment program, and therapeutic alliance measures at intake and discharge for all clients.

Clinicians are provided with a half-day tutorial on the SHADE resource conducted by the research team. The content of this tutorial includes a discussion of the results of the previous clinical trials conducted using the SHADE program, and orientation to the SHADE resource. Clinicians split into groups of two and worked through a different SHADE module on laptops provided by the research team. At the conclusion of this session, clinicians presented each module to the group, and discussed ways in which they felt the module could be integrated into their clinical work at the DACS. Researchers provided their own input into this session where relevant. There was no prescription provided to clinicians as to how, when or with whom the SHADE resource should be used with their clients. However, clinicians suggested that they would use it in the following ways:

(a) “Prescribe” modules for homework in between in-person sessions;

(b) Complete individual modules during the session, sitting side-by-side with clients;

(c) Provide the SHADE resource on DVD-Rom to clients on the wait-list for the DACS;

(d) Use the handouts and worksheets from SHADE to augment discussions about cognitive behavioural skills conducted between clients and clinicians during sessions;

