#### Clients

Following the provision of consent, clients complete the following set of assessment measures at baseline and 12-weeks post-baseline via telephone with a trained research clinician, who is independent of the Central Coast DACS. The following questionnaires take between 30-45 minutes to complete:

(1) Demographics: information includes age, gender, occupational and marital status, children, educational experience, ethnicity and current accommodation arrangements.

(2) Service Utilisation: includes current and previous treatments, including self-reported hospitalisations, attendance at clinics, rehabilitation programmes, contact with community mental health teams, psychologists, psychiatrists, other health professionals, involvement in AOD detoxification and counselling, methadone maintenance, 12-step programmes, use of general practitioners, and use of medication (including compliance).

(3) Opiate Treatment Index 
[24]: a quantity/frequency index to estimate average daily use of 11 drug types (alcohol, marijuana, heroin, other opiates, amphetamines, cocaine, hallucinogens, barbiturates, tranquilisers, inhalants and tobacco) in the month prior to assessment.

(4) Treatment Motivation Questionnaire: is a 26 item self-report measure, examining four components of motivation including internal and external motivation, help seeking and confidence in treatment. A 7-point Likert scale is used to examine the level of motivation.

(5) Depression Anxiety Stress Scale 21-item version 
[25]: a 21-item screening tool to for depression, anxiety and stress in the previous 7 days. A 4-point Likert-type scale is used to determine the extent to which a symptom applied to the person.

(6) Global Assessment of Functioning 
[26]: a clinician-rated assessment of current functioning.

(7) Self-compassion Scale 
[27]: is a 26-item measure using a 5-point Likert-type scale assessing the extent to which a person expresses self-compassion towards themselves in difficult times.

(8) Agnew Relationship Measure – Client Version 
[23]: this client-rated measure of therapeutic alliance is similar in content and structure to the therapist-rated version previously described.

We plan to report the cost of delivering the intervention in real world settings and the cost impacts of the outcomes achieved by calibration of selected instruments used in the study (e.g. Quality of Life Scale, Global Assessment of Functioning) with those achieved in other costing studies.

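### SHADE exposure rests on a clinician checklist assumed half complete, with no second source described, so exposed clients may be misclassified or unclassifiable

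*Protocol article*

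**What the plan says.** All references are to the Protocol article.

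- **Role of exposure.** Study aims hypothesises larger reductions in depression and AOD use in exposed clients. Statistical analyses (Clients) powers an exposed-versus-not comparison at an effect of 0.42 and lists exposure among the regression predictors.
- **Exposure is not assigned.** Under Study design, the study observes SHADE use and clinicians apply it as they see fit.
- **How use is recorded.** The Abstract states: "Clinicians will also complete session checklists following each clinical session with a client, outlining the extent to which the SHADE computer program was used". Study design and Assessments (Clinicians) require this after every session, for exposed and unexposed clients alike.
- **Expected completeness.** Sample size calculation (Clinicians) takes an average of three sessions per client and continues: "Assuming a 50% compliance rate with completion of session checklists by clinicians", "we estimate having a pool of 342 session checklists for analysis".
- **Use outside sessions.** The DVD content may be "provided to clients to complete in their own home in between clinic sessions". One use that clinicians suggested was: "Provide the SHADE resource on DVD-Rom to clients on the wait-list for the DACS". Wait-list clients have not yet been allocated to a clinician.
- **Client side.** Assessments (Clients) lists eight measures ("The following questionnaires take between 30-45 minutes to complete"). None names SHADE. The nearest is Service Utilisation, which covers current and previous treatments in general.

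The article neither defines an exposed client nor says how a client with missing checklists is classified.

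**The concern.** In a randomised trial, allocation is known for everyone. Here the two groups exist only as far as use is written down, and the plan itself budgets for half of the records not being returned. A client who used SHADE in a session without a checklist looks the same as one who never used it. A client with no checklist at all cannot be classified from clinician data.

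Two routes of use lie partly outside the checklist. A DVD given to someone on the wait-list generates no session record at that time. Home use is captured only if it comes up in a later session whose checklist is returned.

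The effect estimate, the regression coefficient for exposure and the reported rate of SHADE use all depend on this one source. A later analysis plan can define exposure and set missing-data rules, but it cannot recover use that nobody recorded.

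**Working it through.** **Inputs from the article:** at most 19 clinicians, 13 clients each (250/19), 3 sessions, 50% checklist completion; effect 0.42 (metric not stated); N = 72 with power 0.81; regression N = 98; 100 clients retained.

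**Assumptions, not in the article:** completion independent across sessions and unrelated to exposure or outcome; no false positives; true exposed share p = 0.25, 0.50 or 0.75.

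**1. The plan's own figures.** Checklist pool: 19 × 13 × 3 × 0.5 = 370.5, not 342. The stated 342 equals 19 × 12 × 3 × 0.5, so it uses 12 clients per clinician although 13 is stated. This is a small separate slip, and nothing below depends on it. The regression size does reproduce: f² = 0.15, 6 predictors and N = 98 give power 0.80.

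**2. Chance that an exposed client is missed.** With SHADE used in k sessions, P(missed) = 0.5^k: 0.50, 0.25 and 0.125 for k = 1, 2, 3. Sensitivity s = 1 − 0.5^k: 0.50, 0.75 and 0.875.

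**3. If unrecorded use is coded unexposed.** Share of the labelled-unexposed who were exposed = p(1 − s)/(1 − ps). Observed effect = 0.42 × (1 − p)/(1 − ps).

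| p | s = 0.50 | s = 0.75 | s = 0.875 |
|---|---|---|---|
| 0.25 | 0.36 | 0.39 | 0.40 |
| 0.50 | 0.28 | 0.34 | 0.37 |
| 0.75 | 0.17 | 0.24 | 0.31 |

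Example: p = 0.5 and s = 0.5 give 0.42 × 0.5/0.75 = 0.28, with 0.25/0.75 = 33% of the labelled-unexposed in fact exposed.

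*Power at p = 0.5.* The stated 0.81 at N = 72 depends on a within-person correlation that the article does not give, so I take it as stated and scale its noncentrality (8.28) by [(1 − p)/(1 − ps)]² × 4ps(1 − ps). The multipliers are 0.778, 0.600 and 0.333 for s = 0.875, 0.75 and 0.50. Power at N = 72 becomes 0.71, 0.59 and 0.37. At N = 100 it goes from 0.92 to 0.84, 0.74 and 0.49.

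**4. If clients with no checklist are set to missing.** P(no checklist in three sessions) = 0.5³ = 12.5%, leaving 100 × 0.875 = 87.5, about 87. Regression power at N = 87 with the same inputs is 0.74.

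Some dilution remains among clients with partial records. With three sessions, k of them using SHADE, a retained exposed client is mislabelled with probability 0.5^k × (1 − 0.5^(3−k)): 0.375, 0.125 and 0 for k = 1, 2, 3. At p = 0.5 the contamination is 0.375/(0.375 + 0.875) = 30%, 0.125/(0.125 + 0.875) = 12.5%, or nil. The effect is then 0.29, 0.37 or 0.42.

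**5. If all three checklists are required before a client is called unexposed.** Of 50 unexposed clients, 50 × 0.125 ≈ 6 qualify. Detected exposed clients number 50 × 0.50 = 25 to 50 × 0.875 ≈ 44. The total is about 31 to 50, below the 72 required.

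**6. Sensitivity to session count.** Using the team figures under Study setting as if fixed, P(no checklist) is 0.5^2.8 = 14% (cannabis clinic), 0.5^4.5 = 4% (AOD counselling) and 0.5^12 ≈ 0.02% (MERIT, if all mandated sessions are attended).

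**The case against.** A reader might infer that exposed clients *will* be counted as unexposed and the effect *will* be diluted. The article does not support that. No passage codes a missing checklist as unexposed, and such a rule would normally sit in an analysis plan that is not shown. This objection stands, and the dilution figures are therefore conditional.

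A reader might also infer that clients are never asked about SHADE. The article gives topics, not questionnaire items, and Service Utilisation might pick up some use. What can be said is that no listed client measure names it.

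Other points that stand:

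- The 50% is a planning allowance for the size of the checklist pool. The procedure asks for a checklist after every session.
- The exposed share is not in the article. At 25% the loss is small.
- Independent completion is a simplification. If returns cluster by clinician, more clients have no checklist (up to half in the extreme), but those clients are visibly unknown and need not be misclassified.
- If clinicians keen on SHADE return more checklists, or return depends on how the client is doing, the error is differential and dilution is no longer the assured direction.
- MERIT clients, with 12 mandated sessions, offer many chances of detection.
- Giving DVDs to wait-list clients was a clinician suggestion, not a study procedure. The checklist also has places for how multimedia was used and whether it was debriefed, so some home use can be recorded.

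These points limit the size and certainty of the problem. They do not supply a second source of exposure data, and the handling rules tried above all cost sample, leave dilution or both under most settings.

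**Conclusion.** The point holds as a weakness in how exposure is ascertained, not as a demonstrated bias. The key client explanatory variable has one described source, assumed half complete over about three sessions, and some permitted use can fall outside it.

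The size depends on a rule that the article does not state. Coding unrecorded use as unexposed takes 0.42 to 0.28-0.37 at 50% true exposure, 0.36-0.40 at 25% and 0.17-0.31 at 75%. Setting clients without any checklist to missing leaves about 87 of the projected 100, short of the 98 stated for the regression. Both results assume independent, non-differential completion at 50%. Without that assumption the bias could go in either direction. The matter is worth settling before data collection, because the missing information cannot be rebuilt afterwards.

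**What to change.** 1. Add a few SHADE-use questions to the follow-up call: ever used, date first used, setting (clinic, home or wait-list), number of modules. Put them at the end, after the outcome measures and the Global Assessment of Functioning rating, so that the interviewer does not learn exposure from them before rating.
2. Log each DVD handed out by client ID, including those given to wait-list clients. The log records access, not use.
3. Define a client as exposed if either the client's report or a checklist shows use. Classify clients with neither source as unknown, not unexposed.
4. State the rule for clients with only some checklists, and reconcile the pool of 342 with 13 clients per clinician.

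Cost: one to two minutes on a 30-45 minute call, and a simple log. Downsides: client recall error, and no client report from those lost to follow-up, for whom the checklist remains the only evidence of use. The observational design is unchanged.

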### Statistical analyses

#### Clients

For the client sample, primary outcome measures are changes in depression, alcohol and marijuana use between baseline and 12-week follow-up.

Previous research using the SHADE resource among substance users 
[16] has resulted in effect size differences of 0.42 between clients exposed to the SHADE resource versus not on depression, alcohol and marijuana use. Assuming similar effect size differences will apply to the current study, we estimate that a sample size of 72 is required at 15-week assessment to achieve adequate power (power = 0.81) to detect differences of this order using repeated measures analysis of variance with an alpha level of 0.05 (calculated using G*Power, version 3.1.2). Predictors of alcohol use, marijuana use and depression at 15-weeks relevant to the current study (e.g. client rated therapeutic alliance, internal and external motivation and coerced vs non coerced clients, exposure to SHADE) will be modelled using a linear regression analysis. This sample size will also enable us to examine an effect size of 0.15 for a linear multiple regression for these outcome variables, with up to 6 predictors, an alpha level of 0.05 and a power co-efficient of 0.80 (actual sample size required = 98).

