### Study design

This study is designed to observe, and not prescribe, the use of the SHADE computerized treatment program within the Central Coast DACS. Ethics approval for the study has been obtained from several relevant Human Research Ethics Committees, led by the Northern Sydney Central Coast Human Research Ethics Committee (08/HARBR/78/79), and including the University of Newcastle Human Research Ethics Committee (H-2008-0271), and the Macquarie University Ethics Review Committee (Human Research, 0806-125M(R)).

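### The client power statement names 72 as the required size although its own regression needs 98, and power 0.81 at 72 does not follow from the inputs it states

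*Protocol article*

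**What the plan says.** All of the following is in the protocol article.

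- Statistical analyses, Clients, effect: earlier SHADE work "has resulted in effect size differences of 0.42 between clients exposed to the SHADE resource versus not on depression, alcohol and marijuana use". The scale of 0.42 (Cohen's d or f) is not named.
- Same section, power: "we estimate that a sample size of 72 is required at 15-week assessment to achieve adequate power (power = 0.81"), "using repeated measures analysis of variance with an alpha level of 0.05 (calculated using G*Power, version 3.1.2"). Sidedness, the ANOVA effect tested, the correlation between occasions and the group sizes are not given.
- Same section, outcomes: "primary outcome measures are changes in depression, alcohol and marijuana use between baseline and 12-week follow-up". There are therefore two measurements.
- Same section, regression: "This sample size will also enable us to examine an effect size of 0.15 for a linear multiple regression", with up to six predictors, alpha 0.05 and power 0.80. The sentence closes with "actual sample size required = 98". The only sample size given before it in that section is 72.
- Sample size calculation, Clients: 250 eligible clients, 50% consent (125) and 80% retention lead to 100 retained clients.
- Study design: "This study is designed to observe, and not prescribe, the use of the SHADE computerized treatment program". Under Clinicians: "There was no prescription provided to clinicians as to how, when or with whom the SHADE resource should be used with their clients".

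**The concern.** Two things look wrong. First, one sentence offers a sample size and then states a larger requirement for the analysis that size is said to support. Second, an effect of 0.42 between two groups is modest, and 0.81 is high power for 72 clients in total unless the repeated measure removes most of the variance.

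The stake is interpretation. The study hypothesises larger reductions in depression and AOD use among exposed clients. If it finds no difference, readers will weigh that against a claimed power above 80% at 72 clients. If the claim rests on an optimistic or mis-scaled input, a null result will look more informative than it is. Naming 72 as the requirement could also let a retained sample well under 98 pass as adequate for the regression.

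**Working it through.** **1. Regression.** Inputs from Statistical analyses, Clients: effect size 0.15 (read as Cohen's f²), 6 predictors, alpha 0.05. Noncentral F with λ = f² × N on 6 and N − 7 degrees of freedom.

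| N | λ | df | Power |
|---|---|---|---|
| 98 | 14.7 | 6, 91 | 0.804 |
| 72 | 10.8 | 6, 65 | 0.63 |
| 100 | 15.0 | 6, 93 | 0.81 |

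The stated 98 reproduces, which confirms the f² reading. The projected sample is 250 × 0.50 × 0.80 = 100, two above 98. Keeping 98 of 125 needs retention of 98/125 = 78.4%, against the 80% assumed.

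**2. Power for 0.42 at N = 72.** Read 0.42 as d in raw SD units, with share s exposed, correlation ρ and a two-sided test. Neither s nor ρ is in the document, so both are assumptions.

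- Change score: λ = d² / [2(1 − ρ)] × N s(1 − s). With s = 0.5 and ρ = 0.5, λ = 0.1764 / 1 × 18 = 3.18, and power is **0.42**.
- ANCOVA: λ = d² / (1 − ρ²) × N s(1 − s) = 0.1764 / 0.75 × 18 = 4.23, and power is **0.53**.
- If 0.42 is already in units of the SD of change, λ = 0.1764 × 18 = 3.18 and power is 0.42 whatever ρ is.

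**3. Which settings give 0.81 at N = 72?**

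- Change score: ρ of about 0.80 to 0.81 (0.794 and 0.813).
- ANCOVA: ρ of about 0.78 to 0.79.
- G*Power within-between interaction with f = 0.42/2 = 0.21: λ = f² × N × 2 / (1 − ρ). At ρ = 0.5 this gives 0.94. At ρ = 0.23, λ = 0.0441 × 144 / 0.77 = 8.25 and power is 0.81.
- 72 per group, one-sided t test: 0.806. This needs 144 clients, more than the projected 100.
- Reading 0.42 as f gives 0.98 (between effect) or above 0.99 (interaction) at ρ = 0.5.

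**4. What the interaction setting implies.** With two groups and two occasions, a difference in change of D raw SDs has cell interaction effects of ± D/4, so f = D/4. Then f = 0.21 means D = 4 × 0.21 = 0.84, twice 0.42. Check: 0.84² / (2 × 0.77) × 18 = 8.25, the same λ as above. For a true difference in change of 0.42 SD at ρ = 0.23, λ = 0.1764 / 1.54 × 18 = 2.06 and power is 0.29.

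**5. Power for d = 0.42 at the projected N = 100, change score, two-sided.** Formula as in step 2.

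| Exposed : not exposed | ρ = 0.5 | ρ = 0.7 | ρ = 0.8 |
|---|---|---|---|
| 50:50 | 0.55 | 0.77 | 0.91 |
| 20:80 | 0.38 | 0.57 | 0.75 |

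ANCOVA at 50:50 and ρ = 0.5 gives 0.67.

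**The case against.** The strongest reply is that 0.81 has not been shown to be a miscalculation. The article does not give d or f, the effect tested or the correlation, and a journal article often leaves software inputs to the full protocol. Some admissible inputs do return 0.81 at 72. The correlation of 0.5 is a reviewer's assumption. At N = 100 with even groups, change-score power is 0.77 at a correlation of 0.7 and 0.91 at 0.8. This stands. A reader might infer that the real power is about 0.42 and the published figure simply wrong; the documents do not support that, because they give no correlation.

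A reader might also infer that the regression is planned to be underpowered. It is not: 72 is the minimum for one analysis, the sentence itself gives 98, and 100 retained clients are projected. What remains is a contradictory sentence and a thin margin.

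On exposure, no ratio is stated, so an even split is an inference about the calculation. Mild imbalance costs little: in the interaction setting that yields 0.81, a 40:60 split at N = 72 still gives 0.79. Only strong imbalance does real damage, and the documents do not predict it.

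Finally, it is tempting to call powering the overall R² an error. It is a legitimate choice for a model of several predictors, and it is calculated correctly.

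The reply does not rescue the power sentence. It publishes a specific figure for differences of the stated size. The routes to 0.81 need a high correlation across three different outcomes that nothing in the document supports, a difference in change twice that size, or twice the clients.

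**Conclusion.** The point holds in two parts.

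- **Certain, given f² = 0.15:** the text contradicts itself. The regression has power 0.63 at 72 and 0.80 at 98. The projected 100 gives 0.81, so the defect lies in naming 72 as the size that serves both analyses, with a margin of two clients once that is corrected.
- **Conditional:** power 0.81 at 72 for 0.42 is unsupported by the stated inputs. With d = 0.42, even groups, two-sided alpha 0.05 and a correlation of 0.5, it is 0.42 or 0.53 depending on the analysis. How far the power at the projected 100 falls short, if at all, depends on the correlation and the exposure split, neither of which the document fixes.

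The correction is worth making because readers will rely on these figures when judging a null result.

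**What to change.** Make three changes in Statistical analyses, Clients.

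1. In the regression sentence, replace the reference to the preceding sample size with the projected 100 retained clients, and give 98 as the minimum.
2. Name the metric of 0.42, the effect tested, the sidedness and the assumed correlation. Restate power at 100 instead of 72.
3. Give a range of correlations and exposure splits, since clinicians decide who is exposed. Possible wording: *For a standardised mean difference of 0.42 (two-sided alpha 0.05, change scores), 100 retained clients give power of 0.55, 0.77 and 0.91 at baseline to follow-up correlations of 0.5, 0.7 and 0.8 if half are exposed, and 0.38, 0.57 and 0.75 if one in five is exposed.* If the sponsor has correlations from its earlier trial, use those instead.

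Optionally, add power for the SHADE coefficient beside the overall R² figure. With f² = 0.42²/4 = 0.044, an even split and no outcome variance explained by the other predictors, it is 0.55 at 100, and about 180 clients would be needed for 0.80.

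The cost is a few sentences and a less favourable power statement. No extra clients are needed and the design does not change.

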## Methods/design

### Study aims

The purpose of this original research is to test the effectiveness of the SHADE computerized treatment program, from both a clinician and client perspective, within the real world clinical setting. It is hypothesised that clients exposed to the SHADE program will report superior reductions in depression and AOD use relative to those who are not exposed, and that this response may be moderated by primary drug of concern (e.g. marijuana vs. other drug use), coercion into treatment and computer comfort. It is also hypothesised that there will be an association between clinician openness to innovation, clinician computer comfort and the use of SHADE in clinical practice.

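### The regression that sets SHADE exposure beside covariates models the 15-week level and does not name the baseline value of the outcome, so a baseline gap between clinician-chosen groups would carry into the SHADE coefficient

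*Protocol article*

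**What the plan says.** Study aims in the protocol article gives the hypothesis as a difference in reductions: "clients exposed to the SHADE program will report superior reductions in depression and AOD use relative to those who are not exposed". Statistical analyses, Clients, is consistent with this: "primary outcome measures are changes in depression, alcohol and marijuana use between baseline and 12-week follow-up".

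That section then describes two client analyses:

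- **Repeated measures analysis of variance**, powered for the comparison of exposed with unexposed clients (effect size 0.42, 72 clients, power 0.81).
- **Linear regression**, introduced as "Predictors of alcohol use, marijuana use and depression at 15-weeks relevant to the current study", with the list "e.g. client rated therapeutic alliance, internal and external motivation and coerced vs non coerced clients, exposure to SHADE) will be modelled using a linear regression". It is sized to detect an effect of 0.15; the other inputs are given as "with up to 6 predictors, an alpha level of 0.05 and a power co-efficient of 0.80 (actual sample size required = 98".

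Exposure is not assigned. On the tutorial for clinicians, Study design says: "There was no prescription provided to clinicians as to how, when or with whom the SHADE resource should be used". Assessments, Clients, has the same instruments completed at baseline and at follow-up, so each outcome has a baseline value.

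**The concern.** The regression is the only stated client model in which SHADE exposure appears with other covariates, so readers are likely to take its coefficient as the adjusted SHADE effect. The outcome is a follow-up level, and none of the named predictors (alliance, motivation, coercion) measures baseline severity. Without baseline in the model, the coefficient compares where clients end up, not how far they have moved. The two agree only if both groups start level.

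Nothing in the design makes them start level. Clinicians choose the clients, and they work in three teams, one of them a marijuana clinic (Study setting). Uneven uptake across teams would directly give unequal baseline marijuana and alcohol use. If more severe clients are given SHADE, a real benefit is masked or looks like harm. If milder clients are given it, a benefit can appear where there is none. The regression could then disagree with the ANOVA on the same data.

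**Working it through.** **1. The plan's own regression figure.** Inputs from Statistical analyses, Clients: effect size 0.15 (read as Cohen's f², an assumption), u = 6 predictors, alpha 0.05, power 0.80. The overall F test has noncentrality 0.15 × N on (u, N − u − 1) degrees of freedom. Power is 0.798 at N = 97 and 0.804 at N = 98, so 98 reproduces.

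**2. Effect of adding baseline on that figure.** As one of the six, N stays at 98 (power 0.813 at the projected 100). As a seventh, N rises to 103 and power at 100 is 0.785. These powers are for the overall test, as in the plan.

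**3. Bias from a baseline gap.** The documents give no gap, exposure split or correlation. Assumed: 50 exposed and 50 unexposed, within-group SD 1 at both times, correlation rho, exposed clients worse at baseline by *gap*, other predictors left out. Two mechanisms are considered:

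- *Selection on baseline severity*: follow-up depends on the client's own baseline, so an expected rho × gap remains at follow-up.
- *Stable group difference*: the whole gap persists to follow-up.

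Expected SHADE coefficient when there is no true effect:

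| Model | Selection on severity | Stable difference |
|---|---|---|
| Level only | rho × gap | gap |
| Level with baseline | 0 | (1 − rho) × gap |
| Unadjusted change | −(1 − rho) × gap | 0 |

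Standard errors at rho = 0.5, gap = 0.5:

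- Level only: √(1/50 + 1/50) = 0.200.
- Change: √(2(1 − 0.5)) × 0.200 = 0.200.
- Level with baseline: √(1 − 0.5²) × 0.200 × √(1 + 0.5²/4) = 0.866 × 0.200 × 1.031 = 0.179.

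Bias and two-sided false rejection at nominal 5% (t tests; simulation agrees):

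| Model | Selection on severity | Stable difference |
|---|---|---|
| Level only | +0.25 SD, 24% | +0.50 SD, 70% |
| Level with baseline | 0, 5% | +0.25 SD, 28% |
| Unadjusted change | −0.25 SD, 24% | 0, 5% |

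**4. Sensitivity.** Under selection on severity with gap 0.5, level-only false rejection is about 10%, 23% and 41% in simulation at rho 0.3, 0.5 and 0.7. At rho 0.5 it is 8% for gap 0.2 and 11% for gap 0.3. Under a stable difference, gaps of 0.2, 0.3 and 0.5 give 17%, 32% and 70% whatever rho is.

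**5. Masking.** Take a true extra reduction of 0.42 SD (the plan's 0.42 read as SD units), gap 0.5, rho 0.5. Under selection on severity the level-only estimate is −0.42 + 0.25 = −0.17, detected about 13% of the time. With baseline the estimate is −0.42, detected about 65% of the time. Under a stable difference the level-only estimate is −0.42 + 0.50 = +0.08, the wrong sign.

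**6. Level or change once baseline is included.** If level = a + b × exposure + c × baseline, then level − baseline = a + b × exposure + (c − 1) × baseline. The exposure coefficient b is the same, so what matters is whether baseline is in the model.

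**The case against.** Three objections carry weight.

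*The model is not fixed.* The predictor list opens with e.g., up to six predictors are allowed, and about five are named (counting internal and external motivation separately). Baseline could be the sixth, and a fuller analysis plan may say so. A reader might infer that the plan excludes baseline and therefore tests equal levels at follow-up. The text does not establish that. What remains is that nothing reserves the slot, and Study aims names primary drug and computer comfort as possible moderators that could compete for it.

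*The change hypothesis has a matching analysis.* A reader might infer that the plan tests the wrong hypothesis altogether. It does not: the exposed-versus-unexposed comparison is powered on the repeated measures ANOVA, whose group-by-time term compares changes. The regression is a second analysis, presented as a model of predictors. This limits the weight of the point but does not remove it, because SHADE exposure is one of those predictors.

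*Switching to change scores is no cure.* It is tempting to make change the regression outcome because the primary outcome is a change. Under selection on severity, unadjusted change is as biased at rho 0.5 as the level-only model, in the opposite direction: regression to the mean would look like a SHADE benefit. The 70% for the level-only model and the 5% for change both require the gap to persist unchanged. The documents do not say which mechanism holds.

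**Conclusion.** The point holds in a limited form. The regression as written does not secure the baseline value of its own outcome, and with exposure chosen by clinicians a baseline gap would bias the SHADE coefficient under either mechanism. In the illustration (100 clients, even split, rho 0.5, gap 0.5 SD), level-only false rejection lies between about 24% and 70%. Baseline adjustment brings this to 5% and 28%: it removes the bias under selection on severity and halves it under a stable difference. The gap, split and correlation are assumptions, and smaller gaps give smaller errors. Confounding by things other than baseline severity would remain in any of these models.

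The stated 98 is correct for its inputs, and the ANOVA is untouched by this point. That the section uses 12 weeks for the primary outcome and 15 weeks for the analyses is a separate inconsistency that needs reconciling.

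**What to change.** In each of the three regressions (depression, alcohol use, marijuana use), name the baseline value of the same outcome as a fixed predictor and count it among the six. State that a SHADE coefficient from a model without it will not be interpreted as evidence on SHADE. Report the change comparison from the repeated measures ANOVA beside it as a sensitivity analysis, and say that which of the two is less biased depends on how clients come to be exposed. Unadjusted change should not replace baseline adjustment as the lead regression model.

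The cost is wording and one predictor slot. No new data are needed, and 98 stands. If six other predictors are wanted as well, the requirement becomes 103, just above the projected 100.
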